# Rationale and design of the HEALTHY-CATH trial: A randomised controlled trial of Heparin versus EthAnol Lock THerapY for the prevention of Catheter Associated infecTion in Haemodialysis patients

**DOI:** 10.1186/1471-2369-10-23

**Published:** 2009-08-20

## Abstract

**Background:**

Catheter-related bacteraemias (CRBs) contribute significantly to morbidity, mortality and health care costs in dialysis populations. Despite international guidelines recommending avoidance of catheters for haemodialysis access, hospital admissions for CRBs have doubled in the last decade. The primary aim of the study is to determine whether weekly instillation of 70% ethanol prevents CRBs compared with standard heparin saline.

**Methods/design:**

The study will follow a prospective, open-label, randomized controlled design. Inclusion criteria are adult patients with incident or prevalent tunneled intravenous dialysis catheters on three times weekly haemodialysis, with no current evidence of catheter infection and no personal, cultural or religious objection to ethanol use, who are on adequate contraception and are able to give informed consent. Patients will be randomized 1:1 to receive 3 mL of intravenous-grade 70% ethanol into each lumen of the catheter once a week and standard heparin locks for other dialysis days, or to receive heparin locks only. The primary outcome measure will be time to the first episode of CRB, which will be defined using standard objective criteria. Secondary outcomes will include adverse reactions, incidence of CRB caused by different pathogens, time to infection-related catheter removal, time to exit site infections and costs. Prospective power calculations indicate that the study will have 80% statistical power to detect a clinically significant increase in median infection-free survival from 200 days to 400 days if 56 patients are recruited into each arm.

**Discussion:**

This investigator-initiated study has been designed to provide evidence to help nephrologists reduce the incidence of CRBs in haemodialysis patients with tunnelled intravenous catheters.

**Trial Registration:**

Australian New Zealand Clinical Trials Registry Number: ACTRN12609000493246

## Background

Central venous catheterization is an increasingly common method of providing rapid, temporary access for the provision of haemodialysis (HD) to patients with serious acute or chronic kidney failure. Unfortunately, the clinical usefulness of this method is severely limited by the frequent occurrence of bloodstream infections in up to 40% of cases [1-4]. A number of registry [5,6] and observational cohort studies [7] have indicated that there has been an increasing reliance on haemodialysis catheters in incident haemodialysis patients ranging from 30% of patients in Europe and Australia to 60% in the United States of America [8-14]. Hospital admissions for catheter-related bacteraemias (CRBs) have doubled in the last decade [15] and a recent analysis of the Dialysis Morbidity and Mortality Wave 2 study [16] identified initial dialysis access as the main antecedent of bacteraemia in dialysis patients. Recent studies have further suggested that the use of haemodialysis catheters is associated with a 1.5- to 3-fold increase in both all-cause and infectious mortality [17-19].

Blood stream infections can result from extraluminal (exit site or tunnel infections) or intraluminal infection of the catheter [20]. Strategies for preventing CRBs have generally focused on cutaneous antisepsis, topical antibiotic application, antibiotic lock solutions and the use of devices coated or impregnated with antimicrobial agents [21,22]. However, these prophylactic strategies have been limited by concerns about antibiotic toxicity and the appearance of antibiotic-resistant microbial isolates [23,24]. Sodium citrate locks have also been investigated for prophylaxis against CRBs [25], although increased rates of catheter thrombosis have been reported [26].

Locking of catheters with ethanol is a promising technique in this respect as the agent is bactericidal, has low toxicity, is unlikely to produce resistant organisms, is able to disinfect organisms in biofilms, and is cheap. Ethanol is an antiseptic agent which is bacteriocidal by protein denaturation and is active against a wide variety of organisms including Gram-positive bacteria, Gram-negative bacteria, and fungi. In vitro studies have been published demonstrating the bactericidal effect of 70% ethanol against plastic-adherent organisms that commonly cause line infections [27]. Complete eradication of Gram-negative bacilli, Gram-positive cocci, and *Candida albicans *biofilms occurred with 30 minutes treatment with 60% ethanol compared to no eradication with trisodium citrate 46.7%.

The effects of catheter exposure to ethanol have been assessed and published. Silicone dialysis catheter integrity is maintained as assessed by scanning electron microscopy, even after 15 days exposure to 95% ethanol solutions [28]. The amount of silicone released was not significantly different when the catheter was submerged in ethanol compared to 0.9% sodium chloride. Mechanical testing of polyurethane and silicone catheters exposed to ten weeks of 70% ethanol proved ongoing structural integrity of both catheter types after prolonged ethanol exposure [29].

Published data has also demonstrated the effectiveness of ethanol lock therapy in the prevention of CRBs in haematology inpatients [16]. A short daily lock in haematology inpatients was used, which is not practical for long term use in renal dialysis outpatients. The current study is designed to ask whether a weekly lock could reduce the rate of CRBs in haemodialysis outpatients.

## Methods/design

Ethics approval for the trial has been obtained from the Princess Alexandra Hospital Human Research Ethics Committee prior to study initiation and patient enrolment. The study will be performed in accordance with the 2000 Edinburgh, Scotland Revision of the Declaration of Helsinki, the National Health and Medical Research Committee (NHMRC) Statement on Human Experimentation, Joint NHMRC/AVCC Statement and Guidelines on Research Practice, applicable ICH guidelines and the Therapeutic Goods Administration (TGA) – Note for guidance on good clinical practice (CPMP/ICH/135/95) annotated with TGA.

### Participants

Participants will be selected from patients undergoing haemodialysis with incident and prevalent tunnelled intravenous catheters (Fig. 1). Inclusion criteria will include the presence of a tunnelled intravenous catheter and the ability to give informed consent. Exclusion criteria will include:

**Figure 1 F1:**
[figure not shown]
**Schema for the Ethanol Lock Trial**.

1. Pregnancy or breast-feeding

2. Religious or personal objection to the use of ethanol

3. Intolerance to ethanol

4. History of an exit site, tunnel or blood stream infection associated with the current catheter

### Study Design

The study will follow a prospective, open-label, randomised, controlled design. Adequate allocation concealment will be ensured using a centralised computer-generated block randomisation procedure. Randomisation will occur on the day that trial consent is obtained and will be conducted by calling a centralised number to allocate the patient to a trial arm. Stratification will occur for incident versus prevalent catheters.

### Experimental Intervention

Patients in the experimental arm will receive weekly instillation of 3 mL intravenous-grade 70% ethanol into each lumen of the catheter. Ethanol (Dehydrated alcohol USP injection, Phebra Pty Ltd, NSW 2066, Australia) is registered in Australia as an adjunct in the treatment of acute methanol and ethylene glycol poisoning and is supplied as a sterile solution of no less than 96.8% w/w of ethanol. Ethanol is diluted to 70% with sterile Water for Injections BP (Pfizer Australia Pty Ltd, NSW 2114 Australia) in a syringe prior to insertion into the catheter lumen. Dual lumen catheters receive 2 × 3 mL 70% ethanol, equivalent to 0.42 standard alcohol units. The ethanol lock is inserted immediately at the end of a haemodialysis session and left in situ until the next dialysis session (48 hours). When the patient returns for a further dialysis session, the ethanol lock will be aspirated out of each lumen of the catheter. For the remainder of the week patients in the experimental arm will receive standard heparin locks (Heparin sodium 5000 U/mL, Hospira, Germany).

### Control Intervention

Patients in the control arm will only receive the standard heparin lock into each lumen.

### Concurrent Treatments

Patients in each trial arm will undergo standard exit site and other management, as per the haemodialysis unit protocol. This will include thrice weekly exit site application of Medihoney (Medihoney™ Antibacterial Wound Gel, Medihoney Pty Ltd, Brisbane, Australia).

### Blinding

Blinding of investigators and patients is not possible as the distinctive odour of 70% ethanol is immediately recognisable and unable to be concealed. Outcome assessment based on standardised and objective criteria will be performed by persons blinded to treatment allocation.

### Outcome Measures

The primary outcome measure will be time to the first episode of CRB. CRB will be defined using standard objective criteria [30-32]: (a) probable catheter-related bacteraemia requires the isolation of a recognised pathogen from at least one set of blood cultures (or a potential skin contaminant from at least two sets of blood cultures) in the setting of clinical manifestations of sepsis with no other apparent source of sepsis other than the catheter; (b) definitive catheter-related bacteraemia requires the criteria of probable catheter-related bacteraemia and one of: purulence at the exit site; clinical sepsis that responds to antibiotic therapy upon catheter removal (after being refractory prior to catheter removal); or isolation of the same organism from the removed catheter tip.

Secondary outcomes will include:

a. Incidence of CRB caused by different pathogens

b. Time to exit site infection

c. Time to infection-related catheter removal

d. Time to catheter removal

e. Adverse reactions

f. Quality of life

g. Economic cost

### Clinical Assessment of Outcome

Reasons for removal of catheters will be assessed by medical staff. Blood cultures will only be taken as clinically indicated. The results of blood cultures collected during the study period will be recorded by research staff. Complications associated with lock therapy will be assessed on a weekly basis by nursing assessment. Patients will also be assessed for quality of life using the EQ-5D questionnaire, which will be administered by the study nurse on a monthly basis. They will also complete this questionnaire if admitted to hospital during their involvement in the trial. Data will be collected on health care service utilization external to the hospital (such as general practitioner visits) to allow economic evaluation in addition to the hospital-associated costs during the trial.

### Monitoring for Adverse Events

The number and proportion of subjections who report treatment-emergent adverse events will be summarised for each group.

A trial Safety and Data Monitoring Committee has been set up to allow external evaluation of catheter-related problems at 6 months and annually after that period. This will consist of Renal and Infectious Diseases Physicians not otherwise involved in the study, who will assess the significance of catheter-associated problems in the treatment vs control group.

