### Sample Size Calculations

Prospective power calculations indicate that the study will have adequate statistical power (80% probability) to detect a clinically significant increase in infection-free survival from 200 days to 400 days if 56 patients are recruited into each arm (total 112 patients). These assumptions are based on local data in haemodialysis patients at the Princess Alexandra Hospital. A recruitment period of 3 years is anticipated.

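### Adverse events are summarised only as proportions of patients, so if ethanol prolongs catheter life, lock- and catheter-related events could look more frequent on ethanol at equal rates per catheter-day

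*Protocol article*

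**What the plan says.** In the protocol article, Monitoring for Adverse Events gives one measure: "The number and proportion of subjections who report treatment-emergent adverse events will be summarised for each group". The denominator is patients. No time at risk and no test is named.

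The same section sets up an external committee of physicians "who will assess the significance of catheter-associated problems in the treatment vs control group", with "external evaluation of catheter-related problems at 6 months and annually after that period".

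Clinical Assessment of Outcome adds that "Complications associated with lock therapy will be assessed on a weekly basis by nursing assessment". It does not say when these assessments stop.

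The abstract plans for an "increase in median infection-free survival from 200 days to 400 days". Outcome Measures lists adverse reactions as a secondary outcome, beside time to catheter removal for any cause and for infection. Statistical Analyses describes Kaplan-Meier curves with censoring at study completion and at non-infective catheter removal, for infection-free survival. It applies intention to treat to all data.

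**The concern.** A lock complication or a catheter thrombosis needs a catheter in place. If ethanol works and fewer catheters are removed for infection, the ethanol arm has more catheter time in which such events can occur and be recorded. The proportion of patients with at least one event rises with time at risk, even when the rate per catheter-day is the same in both arms. The distortion can also run the other way: if ethanol catheters came out early, the proportion would understate harm.

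The infection and removal outcomes are defined as times, so differing follow-up is handled there. The stated safety measure does not handle it. Safety is an explicit purpose of the trial: the Discussion undertakes to assess adverse events prospectively and singles out catheter thrombosis, which was a problem with another lock solution. The committee's task is comparative, so its members would probably read such figures side by side.

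**Working it through.** **The plan's own figure.** The article gives no figure for adverse events. Its sample size can be checked, to confirm that an exponential reading of the medians is reasonable. With hazard ratio 200/400 = 0.5, two-sided 5% and 80% power, Schoenfeld's formula gives 4 × (1.960 + 0.842)² / (ln 2)² = 65.3, so 66 events. If each patient is followed for 365 days (an assumption, since follow-up is not stated), the event probabilities are 0.718 and 0.469, mean 0.593, and 66/0.593 = 111.3, so 112 patients. This matches the stated total of 112. It does not bear on safety beyond supporting the model.

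**Inputs from the article.** Medians 200 v 400 days, so the hazards of bacteraemia per day are λ = ln 2/200 = 0.003466 (heparin) and ln 2/400 = 0.001733 (ethanol); 56 patients per arm; 3 years' recruitment.

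**Assumptions.** The same constant adverse-event hazard *a* in both arms, at 0.2, 0.5 or 1.0 per year. Observation ends at bacteraemia, at non-infective removal (hazard *c*) or at study end. Three follow-up patterns: uniform entry over 3 years with analysis at its close, 1 year each, or 3 years each. The true rate ratio is 1.0 throughout.

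**Formula.** With h = a + λ + c and follow-up u, P(at least one event) = (a/h) × (1 − e^(−hu)). For uniform entry over A = 1095 days this averages to (a/h) × [1 − (1 − e^(−hA))/(hA)].

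**Worked case: uniform entry, no other removal, one event per year** (a = 1/365.25 = 0.002738).
- Heparin: h = 0.006204, a/h = 0.4413, bracket = 1 − 0.1470, so P = 37.6%.
- Ethanol: h = 0.004471, a/h = 0.6124, bracket = 1 − 0.2027, so P = 48.8%.
- Crude ratio 1.30. Mean observed time is 214 v 319 days, ratio 1.49.

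**Range over the three follow-up patterns and three event rates**

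| Non-infective removal | Mean-time ratio | Crude ratio of proportions |
|---|---|---|
| none | 1.31 to 1.74 | 1.25 to 1.64 |
| median 400 days | 1.27 to 1.47 | 1.21 to 1.42 |
| median 200 days | 1.23 to 1.33 | 1.19 to 1.30 |
| median 60 to 100 days | 1.12 to 1.20 | 1.10 to 1.19 |

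The largest value, 1.64, is 13.5% v 22.0% (0.2 events per year, 3 years each, no other removal). Rarer events bring the crude ratio closer to the ratio of mean times.

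**Chance of a nominally significant excess on ethanol**, if someone tested the proportions with 56 per arm (the plan names no test): 7% to 42% with no other removal, and about 3% to 10% with removal at a median of 60 to 200 days.

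**Unlimited follow-up**, as an upper reference at one event per year: P = a/h, giving 44% v 61% with no other removal, 34.5% v 44% at a removal median of 400 days, and 28% v 34.5% at 200 days.

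**First committee review.** With uniform entry over the first 6 months, one event per year and no other removal, the proportions are 17.7% v 19.4%, and mean time is 75 v 82 days (ratio 1.10). The effect is small at that look and grows later.

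**With a time-based measure**, the rate ratio per catheter-day is 1.00 in every row, by construction. If instead patients stay at the same risk to a common end after bacteraemia, the crude ratio is also 1.00.

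**The case against.** A reader might infer that ethanol would look less safe merely because it worked. The documents do not support that, for four reasons.

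- **End of observation.** No section says that adverse-event collection stops at bacteraemia or catheter removal. The censoring rule belongs to the infection-free survival analysis. Bacteraemia and infection-related removal are separate outcomes, so bacteraemia need not end catheter use. This stands, and it makes the size conditional. It does not remove the point: once a catheter is out and not replaced, lock complications and catheter thrombosis cannot occur, so follow-up to a common end still leaves unequal time at risk for those events.
- **Summary, not test.** The article plans to summarise by group and names no test. Nor does it say that the committee sees only crude proportions. Both stand. The between-arm reading follows from the committee's stated task.
- **Direction.** An all-cause count would include infection-related events, which would be more frequent on heparin if ethanol works. If reactions cluster at the first instillations, extra exposure hardly matters, and a rate per catheter-day would dilute harm in the longer-exposed arm. Both stand. The first limits the point to lock- and catheter-related events, and the second is why a rate alone is not enough.
- **Another document.** A full protocol or SAP may add exposure-adjusted rates, and a number with a proportion is a conventional description. This also stands, so the point is an improvement to a stated measure and not the correction of an error.

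Early failure of ethanol catheters is partly covered already, because time to catheter removal is an outcome and reasons for removal are assessed.

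**Conclusion.** The point holds in a limited form. The only adverse-event measure stated ignores time at risk, in a trial whose hypothesis implies that catheter time may differ by arm. Crude proportions of lock- and catheter-related events could therefore make ethanol look less safe at equal rates.

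Under constant, equal event hazards, and with observation ending at bacteraemia or catheter removal, the apparent ratio is about 1.1 to 1.3 when non-infective removal has a median of 60 to 200 days. It is up to about 1.6 with no such removal, and a 400-day median falls between. The larger contrasts, such as 44% v 61%, need unlimited follow-up and no other removal, whereas the article expects both study completion and non-infective removal to end observation. Event rates, removal rates and the end of adverse-event collection are all assumed here. This is an inexpensive improvement and does not affect the primary analysis.

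**What to change.** 1. State when adverse-event collection ends: at bacteraemia, at catheter removal or at a common study end, and what happens if a catheter is replaced.
2. Keep the number and proportion of patients as description.
3. For lock- and catheter-related events, add the rate per 1000 catheter-days in each arm, with a rate ratio and 95% CI.
4. Add cumulative incidence to first event over catheter time, to show any early clustering that a single rate would dilute. Censor at the end of catheter time for this purpose, because counting removal as a competing event would bring the exposure difference back in.
5. Give the monitoring committee the same figures.

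The cost is a few sentences and no new data collection for the denominator: catheter dates are already needed for the two removal outcomes. Dates of first events must be recorded, to the week at least, which the weekly assessments allow.

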### Sample Size Calculations

Prospective power calculations indicate that the study will have adequate statistical power (80% probability) to detect a clinically significant increase in infection-free survival from 200 days to 400 days if 56 patients are recruited into each arm (total 112 patients). These assumptions are based on local data in haemodialysis patients at the Princess Alexandra Hospital. A recruitment period of 3 years is anticipated.

### Statistical Analyses

Infection-free survival curves, survival probabilities and estimated survival times will be generated using Kaplan-Meier methodology. Data will be censored at the time of study completion and removal of catheter for non-infective reasons. The first occurrence of a relevant infective event will be considered an event. Differences in the survival curves will be assessed using the log rank test. All data will be analysed on an intention-to-treat basis. P values < 0.05 will be considered significant.

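### Kaplan-Meier with non-infective catheter removal as ordinary censoring overstates the actual probability of CRB in each arm and misstates the absolute difference, in a direction that depends on removal rates by arm

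*Protocol article*

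**What the plan says.** In the protocol article, Outcome Measures defines the endpoint: "The primary outcome measure will be time to the first episode of CRB". Statistical Analyses then fixes three things:

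- Estimator: "Infection-free survival curves, survival probabilities and estimated survival times will be generated using Kaplan-Meier methodology".
- Censoring: "Data will be censored at the time of study completion and removal of catheter for non-infective reasons".
- Test: "Differences in the survival curves will be assessed using the log rank test".

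The same section adds that "All data will be analysed on an intention-to-treat basis". It names no cumulative-incidence estimator and does not mention death. Outcome Measures lists time to catheter removal, and time to infection-related removal, as separate secondary outcomes. Under Clinical Assessment of Outcome, medical staff assess the reasons for removal. No rate of non-infective removal appears anywhere, including in Sample Size Calculations.

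**The concern.** Censoring at study completion and censoring at removal are different in kind. A patient censored at study completion still has a catheter that may later become infected. A patient whose catheter has been taken out has no such risk from that catheter. Kaplan-Meier treats both alike: it assumes that the censored patient would have gone on to CRB at the same rate as those still at risk.

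The result is the risk of CRB in a setting where catheters are never removed for other reasons, and even that holds only if removal is independent of infection risk. It is not the proportion of patients who will have a CRB from the catheter under study. Since the article intends to report survival probabilities and times, a reader would naturally take them as that proportion. Tunnelled catheters are often removed without infection, so the gap may be large. At stake is the correct reading of the absolute risks and their difference.

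**Working it through.** **Inputs from the article.** Median infection-free survival of 200 days (heparin) and 400 days (ethanol), 56 patients per arm, 80% power, 1:1 allocation and 3 years of recruitment.

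**Assumptions.** Exponential times, two-sided 5% level, and a median time to non-infective removal of 100 to 400 days, independent of CRB. The article gives no removal rate.

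**The plan's own figure.** A hazard ratio of 0.5 needs, by Freedman's formula, (1.960 + 0.842)² × (1.5/0.5)² = 70.6 events. With uniform accrual over 1,095 days, follow-up ending when accrual closes and no removal, the event probabilities are 0.742 and 0.552. Then 70.6/(0.742 + 0.552) = 54.6, or 55 per arm. Lachin's formula gives 54. The stated 56 is reproduced within 2 patients, so the exponential reading of the medians is reasonable.

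**Formulas.** λ = ln 2/200 (heparin) or ln 2/400 (ethanol); μ = ln 2/(median time to removal).

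- 1-KM(t) = 1 − exp(−λt)
- Cumulative incidence(t) = λ/(λ+μ) × [1 − exp(−(λ+μ)t)]

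**1-KM at 365 days.** Heparin: 1 − exp(−0.003466 × 365) = 71.8%. Ethanol: 1 − exp(−0.001733 × 365) = 46.9%. Difference: 24.9 points.

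**One cumulative incidence in full (removal median 200 days in both arms).** Heparin: 0.5 × [1 − exp(−2.530)] = 46.0%. Ethanol: (1/3) × [1 − exp(−1.897)] = 28.3%.

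**All cases at 365 days** (differences are from unrounded values):

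| Removal median, heparin / ethanol (days) | Heparin | Ethanol | Difference (points) |
|---|---|---|---|
| 1-KM, any removal rate | 71.8% | 46.9% | 24.9 |
| 400 / 400 | 56.7% | 35.9% | 20.8 |
| 200 / 200 | 46.0% | 28.3% | 17.7 |
| 100 / 100 | 32.6% | 19.2% | 13.4 |
| 200 / 400 | 46.0% | 35.9% | 10.1 |
| 200 / 150 | 46.0% | 24.6% | 21.4 |
| 200 / 100 | 46.0% | 19.2% | 26.9 |
| 400 / 200 | 56.7% | 28.3% | 28.3 |

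**Reading the table.** 1-KM is above the cumulative incidence in every row, by about 15 to 39 points for heparin and 11 to 28 points for ethanol. The difference is overstated when removal is equal, higher under heparin, or modestly higher under ethanol. In the last two rows ethanol doubles the removal hazard, and the difference is understated.

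**Survival times.** With a 200-day removal median, the ethanol cumulative incidence can never exceed λ/(λ+μ) = 1/3, yet Kaplan-Meier would report a median of 400 days.

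**Why removal must be shown beside CRB.** Suppose the lock has no effect on CRB (median 200 days in both arms) but removal medians are 200 and 100 days. Cumulative incidence is then 46.0% versus 32.6%: 13.4 points of apparent benefit that come only from faster catheter loss.

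**The case against.** The strongest reply is that censoring at removal asks a legitimate question: does the lock lower the CRB hazard while the catheter is in place? If removal is independent of infection risk, the log-rank test remains valid for that cause-specific hazard. This stands, and the primary test is not at issue. It is also true that the article is condensed and that a supplementary display, or the handling of death, could sit in the full protocol. But the article itself fixes both the estimator and the censoring rule for the probabilities it will report, so that part is a stated choice.

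A reader might infer more than the document supports:

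- *The absolute benefit is always overstated.* The last two rows of the table show the opposite when ethanol doubles the removal hazard.
- *The log-rank test would produce false wins for ethanol.* That needs removal to differ by arm and also to share causes with infection. In simulations with no true effect, a control removal median of 300 days and a strong shared frailty (SD 1), doubling or tripling removal under ethanol gave roughly 5% and 8-9% false ethanol wins, against a nominal 2.5%. With SD 0.5 the figures were just under 4%, and with independence about 2-3%. If ethanol halved removal, the bias ran against ethanol. The article supports no particular scenario: its remark on thrombosis in the Discussion concerns citrate, and the experimental arm receives heparin locks for the rest of each week.
- *Faster catheter loss would go unseen.* Time to catheter removal is a secondary outcome and reasons for removal are assessed.
- *A number needed to treat or the cost evaluation is distorted.* The article mentions no number needed to treat. It lists "Economic cost" as an outcome based on collected service use and hospital costs, with no link to Kaplan-Meier.

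**Conclusion.** The point holds for the reported probabilities and survival times, and not for the primary test. Followed as written, the plan overstates the actual probability of CRB in each arm whenever non-infective removal occurs. The absolute difference is also misstated, and its direction cannot be settled from the document. The sizes in the table rest on constant hazards, removal independent of infection, and assumed removal medians of 100 to 400 days. The upward bias within each arm does not depend on those particular values; its size does.

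**What to change.** 1. Keep the log-rank test, with the cause-specific hazard ratio, as the primary comparison.
2. Report CRB probabilities as Aalen-Johansen cumulative incidence, with non-infective removal and death as competing events.
3. Label any Kaplan-Meier probability or median as conditional on the catheter staying in place.
4. Beside it, show the cumulative incidence and cause-specific hazard ratio of non-infective removal by arm, so that a lower CRB incidence due to faster catheter loss is not read as prevention. The planned time to catheter removal covers all causes, so it does not replace this.
5. Do not use Gray's test or a Fine-Gray hazard ratio as evidence of efficacy. Both would credit an arm for losing catheters sooner.

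Cost: a small additional analysis, using removal dates and reasons already collected. The reported CRB risk in each arm will be lower than under Kaplan-Meier. The sample size and the primary test do not change.
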